## Methods

### Research Design

The ACE Study is a stepped-wedge cluster (nested) randomized controlled, investigator-blinded, multicenter, non-inferiority trial with parallel intervention groups. The rationale for this trial design (Phase 1, a period where the control group data will be collected, and Phase 2, randomization of participants to either the midwife [MW] or video instruction [VI] groups) was chosen as it provides a quarantined period of observation and data collection from the control group. Randomizing participants to all three groups simultaneously was not performed as this would risk contamination (via artificially increasing knowledge above standard care) in the control group and hospital staff delivering care. Pregnant individuals attending the same antenatal classes may discuss and share aspects of their care, and hospital staff may inadvertently promote ACE to the control group. Each hospital (site) is a cluster, with the Phase 1 start time being dependent on hospital logistics (for example ability to carry out staff training, ethics, and governance approvals). During Phase 2, nested within each cluster, individual participants are randomized (50:50) to one of two invention arms. The trial has a primary endpoint of 4 months postpartum, specifically the rate of EBF4M. All enrolled participants will have data collected until 4 months postpartum. The endpoint in this trial was chosen as a timepoint where the achievement of the proposed level of breastfeeding would be significant, given previous national indicators (Australian Bureau of Statistics, 2017–2018).

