#### Breastfeeding in Australia

In Australia, National Health Survey data shows that the prevalence of exclusive breastfeeding at 4 months of age is 61%, and drops to 29% by 6 months of age, with rates remaining consistent since 2014 to 2015 (Australian Bureau of Statistics, 2017–2018). The more recent National Health Survey data (2020 to 2021) was collected online during the COVID-19 pandemic and should be used for point-in-time analysis only and not be compared with previous survey data. The National Health Survey data for 2017 to 2018 came from a sample of approximately 21,300 people across Australia. Data was collected during personal interviews. One person was interviewed per household and provided breastfeeding data about one child in the household.

In Australia, those individuals not breastfeeding to 6 months are more likely to be primiparous, overweight or obese, have lower education, and smoke cigarettes (Moss et al., 2020). The primary reasons for not breastfeeding to 6 months in Australia include the perception of insufficient milk supply and other breastfeeding difficulties (e.g., latching issues, pain, expressing is too hard; Moss et al., 2020).

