### Exclusion Criteria

The exclusion criteria are listed in Table 1. Individuals who develop any relevant maternal or infant medical conditions listed as exclusion criteria will not be eligible to participate/will be withdrawn from the trial.

**Table 1. table1-08903344231215074:** PICO (Population, Intervention, Comparison, Outcomes) for the ACE Study.

Study Component	Details
Population	Inclusion criteria
	● Nulliparous individuals
	● Singleton pregnancy
	● Able to read and speak in English
	● Planning to breastfeed
	● Willing to participate in the trial
	● Planning to give birth at one of the trial sites
	Exclusion criteria
	● EPDS score ≥13, or PASS score ≥26
	● Diabetes (pre-existing and pregnancy-induced)
	● Pre-eclampsia
	● Placenta previa
	● Antepartum hemorrhage
	● History of threatened/actual premature labor
	● Cervical incompetence
	● Fetal anomaly (cleft palate, down-syndrome, heart defect, neural tube defects)
	● Fetal compromise (polyhydramnios, known inter-uterine growth restriction)
	● Preterm birth (<37 weeks gestation)
Intervention	Intervention components in addition to standard maternity care during phase 2 include:
	● Oral and written information on antenatal colostrum expression: commence hand expressing from 37 weeks gestation, twice a day for 3-5 minutes per breast (maximum 10 minutes); and information on safe storage of colostrum during pregnancy
	● One-on-one ACE education session with midwife/IBCLC *or*
	● Unlimited access to an online 16-minute ACE instructional video
Comparison	Control group will receive standard maternity care
Outcomes	Primary outcome:
	● Exclusive breastfeeding at 4 months postpartum (EBF4M) [phase 1 control period versus phase 2 ACE groups (combined)]
	● Secondary outcomes:
	● Exclusive breastfeeding at 1, 4, 8, 12, and 16 weeks postpartum [MW intervention group versus the VI intervention group]
	● Exclusive breastfeeding from birth to discharge
	● Time to secretory activation
	● Colostrum composition after birth: macronutrients (lactose, protein, fat content), IgA, soluble CD14, Lactoferrin, EGF, and TGF
	Other outcomes:
	● Maternal attitudes to infant feeding
	● Breastfeeding self-efficacy
	● Time from starting ACE (obtained from milk-expressing diaries) until labor
	● Post-term induction rate
	● Gestational age at birth
	● Infant admission to special care nursery

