**Figure 2. fig2-08903344231215074:**
[figure not shown]
The ACE Study Flowchart. *Note.* EBF = Exclusive breastfeeding; EBF4M = Exclusive breastfeeding a 4 months. *Phase 1 control participants complete a 4-month observation period before recruitment and randomization of intervention participants. **Intervention phase. ^1^Telephone-administered or completed online by participants who cannot complete via telephone.

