### Current Trial Status

The trial is ongoing and in the data collection phase. Recruitment began in September 2019, with an anticipated finish date of end. The last recruited participants are expected to reach the primary endpoint of 4 months postpartum in April 2025. Completion of data analysis is anticipated by the end of 2025.

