## Interventions

### Sequence Generation

The research team is using phased randomization (implemented via the stepped-wedge design), where an observation control group is recruited before commencing the intervention phase at each trial site. During Phase 2 at each trial site, participants have equal opportunity to be randomized into either the MW or VI groups. The randomization process is done using an online program for minimization (via QMinim) to ensure a balance of participants in intervention groups based on the chosen balancing variables. Two different balancing variables are used, maternal age (< 30, ≥ 30 years), and socioeconomic status (low, medium, high; determined by postcode and education level). The biased coin approach (*P* = .7; default in QMinim) is used to determine group allocation.

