## Planned Data Analysis

Data will be analyzed using SPSS (Version 29) or R. The primary outcome variable is EBF4M postpartum (yes or no). The secondary outcome variables are any or exclusive breastfeeding (at 1/4/8/12/16 weeks postpartum—analyzed separately), supplementation with a human milk substitute in the hospital (yes or no), time of secretory activation (≤ 1 day, 2–3 days, or > 3 days postpartum) which are all dichotomous. Other outcome variables are infant admission to SCN (yes or no; dichotomous) and gestational age at birth (continuous). Any or exclusive breastfeeding at 1, 4, 8, 12, and 16 weeks postpartum, use of human milk substitutes in hospital, infant admission to SCN (dichotomous outcomes), and time of secretory activation (nominal outcome) will be assessed (and reported) both using unadjusted analysis (a basic comparison of proportions) and using an adjusted analysis (mixed-effects logistic regression, adjusted for maternal age, socioeconomic status, mode of delivery and potentially other hypothesized confounders). Gestational age at birth (continuous outcome) will similarly be assessed (and reported) both using unadjusted analysis (Student’s *t* test) and adjusted analysis (mixed effects linear regression, if modeling assumptions are met adjusted for maternal age, socioeconomic status, and potentially other confounders). The mixed effects models will incorporate a site variable both as a fixed effect, addressing any inter-site differences, and as a random effect, accounting for any inherent within-site correlation in the data resulting from the clustered design. The decision to include variables as confounders for adjustments in the models is based on both hypothesized and established (from related literature) relationships with the outcomes and variables of interest. An analysis of variance (ANOVA) test will be used to compare two models, one within and one without a site, by intervention interaction variable. If the model with the interaction term is deemed to be a better fit, then only pre-specified subgroup analysis will occur, which is a per-site analysis using the same models as described above. Missing data will be reported (as count and percentage) by variable and group. If problematic, multiple imputation (by chained equations) will be used to impute missing values, with reported effect estimates then calculated by pooling across models run on imputed datasets. A level of significance of *p* < 0.05 will be used, and the research team will use confidence intervals to give context to outcome variability.

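### The primary control-versus-ACE contrast is earlier-versus-later within every hospital, but the analysis names no calendar-time term, so a shared change between phases would bias the ACE effect in either direction

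*Protocol article*

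**What the plan says.** Table 1 and Table 4 of the protocol article define the primary contrast as the Phase 1 control period against the two Phase 2 ACE arms combined, on EBF4M.

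The order of the phases is the same everywhere. Under Sequence Generation the design is one "where an observation control group is recruited before commencing the intervention phase at each trial site". The note to Figure 2 adds that "Phase 1 control participants complete a 4-month observation period before recruitment and randomization of intervention participants". Sites enter at different times, "with the Phase 1 start time being dependent on hospital logistics" (Research Design). Randomization of individuals covers only midwife versus video, within Phase 2.

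Under Planned Data Analysis the adjusted model is mixed-effects logistic regression, "adjusted for maternal age, socioeconomic status, mode of delivery and potentially other hypothesized confounders". On clustering, "The mixed effects models will incorporate a site variable both as a fixed effect, addressing any inter-site differences, and as a random effect". The a priori confounders listed after Table 4 are education, BMI, smoking, city living, attitudes to breastfeeding and paternal support.

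Under Current Trial Status, recruitment began in September 2019 and "The last recruited participants are expected to reach the primary endpoint of 4 months postpartum in April 2025". Limitations expects the design's limitations to fall equally on all three groups and does not mention secular trend.

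**The concern.** In a stepped-wedge design the intervention effect is separated from a shared time trend by modelling time, using the fact that sites cross over at different dates. Here the design carries that name, but the analysis names no time or period term. With site in the model and time left out, each hospital contributes its later ACE women minus its earlier control women. Anything else that changed between those periods goes into the ACE coefficient. A site effect does not remove a trend that all sites share, and recruiting more women does not shrink the bias.

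The primary conclusion of the trial therefore rests on an unstated assumption that EBF4M would have stayed level between phases without ACE. The trial spans the COVID-19 period, which the article itself treats as able to disrupt in-person care, and the article reports growing interest in ACE.

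**Working it through.** **1. The plan's own sample size.** Inputs from Sample Size: 27% versus 45%, 5-point superiority margin, one-sided 0.05, 80% power, intraclass correlation 0.01.

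- Without clustering: n0 = (0.27×0.73 + 0.45×0.55) × (1.645 + 0.8416)² / (0.18 − 0.05)² = 162.7 per group.
- With design effect 1 + (n/K − 1)×0.01: K = 4 sites gives n = 271.4; K = 7 gives 209.8. The article does not state K; four sites reproduces the stated 271.

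This reproduces the stated figure with no allowance for time.

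**2. Separation of the phases (assumed; the article gives no site timelines).** Per site: 6 to 9 months of control recruitment, a 5 to 6 month gap, 12 to 18 months of Phase 2. Distance between phase midpoints:

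- Short: 3 + 5 + 6 = 14 months = 1.17 years.
- Long: 4.5 + 6 + 9 = 19.5 months = 1.63 years.

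**3. Bias and error with no true ACE effect.** Bias = drift × separation. Standard error without time, 271 versus 542 women at 45%: sqrt(0.45×0.55×(1/271 + 1/542)) = 3.7 points. One-sided error against no difference = 1 − Φ(1.645 − bias/3.7). Against the margin, bias is replaced by bias − 5.

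| Assumed drift, points/year | Bias, points | One-sided error vs no difference | One-sided error vs 5-point margin |
|---|---|---|---|
| 1 | 1.2–1.6 | 9–11% | about 0.5% or less |
| 2 | 2.3–3.3 | 16–22% | 1–2% |
| 3 | 3.5–4.9 | 24–37% | 2–5% |

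At a common rate of 27% the standard error is 3.3 points; the error against no difference is then 10–43%, and against the margin still under 5%. A drift of −1 to −3 points per year gives the same biases with the sign reversed.

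A longer assumed schedule (1 year of controls, 4-month gap, 2 years of ACE; midpoints 1.83 years apart) gives biases of 1.8, 3.7 and 5.5 points at the same drifts.

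**4. Cost of adding time.** With site effects and linear time, one third of women in control and two thirds in ACE, the standard error grows by sqrt((B + W)/W). B is the between-phase variance of calendar time, (2/9)×separation². W is the within-phase variance, (1/3)L1²/12 + (2/3)L2²/12, with L1 and L2 the phase lengths in years.

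- Short schedule (L1 = 0.5, L2 = 1): B = 0.302, W = 0.0625, ratio 2.4.
- Long schedule (L1 = 0.75, L2 = 1.5): B = 0.587, W = 0.141, ratio 2.3.

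Fitting 6-month periods instead gave about 2.2 to 2.4 when site starts were at least 4 months apart. The 1.83-year schedule gives a ratio of 2.0; in simulation under it, a linear time term removed a linear drift and held one-sided error at about 4–6%.

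**5. Power with time in the model.** At 27% versus 45%, the standard error without time is sqrt(0.27×0.73/271 + 0.45×0.55/542) = 3.44 points. Multiplied by 2.2 to 2.4 it is 7.6 to 8.3 points. One-sided power is then about 70–77% against no difference and 47–53% against the 5-point margin. Without time, power against the margin is about 98% (no clustering inflation in either figure).

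**The case against.** The covariate list is open-ended and the a priori list is introduced as partial, so a period term is not excluded, and an analysis plan that is not shown might add one. That stands: the accurate statement is that the article names no time term, not that the analysis will have none. It does not dispose of the point, because the article does name its main covariates and site terms, and following them gives a before-after estimate.

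The model sentence does not name EBF4M. It lists breastfeeding at 1 to 16 weeks and other outcomes. Reading it as covering the primary outcome is an inference, from the 16-week outcome and from the abstract, which applies adjusted logistic regression to breastfeeding outcomes generally.

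A reader might infer that every statewide change over 2019–2025 is credited to ACE. The documents do not support that. Only the change between a site's own two phases enters, and a fall would mask a benefit.

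A reader might also infer that drift is documented. It is not. The only trend reported is a stable national rate from 2014–15 to 2017–18, before the trial. The remark that the 2020–21 survey "was collected online during the COVID-19 pandemic and should be used for point-in-time analysis only and not be compared with previous survey data" concerns survey comparability and does not show a change in feeding.

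The 5-point margin absorbs most of the assumed bias if the test uses it. Planned Data Analysis does not repeat the margin, so both readings are shown. Finally, sequential phases have a stated and reasonable purpose, avoiding contamination of controls; the point concerns the analysis, not that choice.

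**Conclusion.** The concern holds as a defect in the analysis as named. The primary contrast is confounded with calendar time at every site, and no named term addresses this. Under the assumed schedules and drifts the bias is about 1.2 to 4.9 points, upward or downward. With an upward drift, one-sided 5% error against no difference becomes about 9% to 37%, and at most about 5% against the 5-point margin.

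These figures rest on assumed phase lengths, an assumed linear drift common to all sites, and an analysed sample of 271 and 542. The documents neither establish nor rule out a drift. The midwife-versus-video comparison is concurrent and randomized, and is not affected.

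The evidence does not justify a rule that ACE may be credited only if the time-adjusted estimate supports it. With the standard error more than doubled and the overlap of site starts unknown, that rule would be a debatable trade-off.

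**What to change.** - Prespecify a calendar-time-adjusted model for EBF4M: site plus 6-month periods where site starts overlap enough, otherwise a linear or smooth time term. State that the latter depends on the assumed shape of the trend, which a pandemic shock need not follow.
- Name EBF4M explicitly in the model sentence, and report the estimates with and without time side by side.
- State the expected precision of the time-adjusted estimate from the actual site start dates, and acknowledge that its power is lower than Sample Size gives.
- Add secular trend to Limitations as one that does not affect the three groups equally.

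The cost is wording and one further model, fitted on recruitment or birth dates that the trial should already hold. The statistical price is a wider interval: a standard error about 2.2 to 2.4 times larger under the assumed schedule. The real figure depends on how far the site starts are staggered.

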### Limitations

There may be some limitations in the design of this trial; however, it is expected that the limitations will affect all three groups equally. First, because the study will be conducted only in English, it will not include non-English speaking participants. This is due to the potential language barrier that may impede the accuracy of communicating the instructions for ACE. Additionally, if participants are unable to fully understand the questions being asked in the postnatal follow-up questionnaires, this will impede the accuracy of the results. Second, there is a risk for recall bias (unintentional and intentional responder bias) resulting from possible sleep deprivation coupled with having a newborn and potential stigma/shame around the inability to breastfeed. Third, participants in the intervention groups are unable to be masked to group allocation due to the nature of the intervention.

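### The primary control-versus-ACE contrast is a non-randomised before/after comparison within each site, and the stated model has no calendar-time term; separately, site is entered twice

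*Protocol article*

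**What the plan says.** **Order of recruitment.** Sequence Generation describes a phased scheme "where an observation control group is recruited before commencing the intervention phase at each trial site". The note to Figure 2 adds that "Phase 1 control participants complete a 4-month observation period before recruitment and randomization of intervention participants". In the described flow, no control at a site is concurrent with an ACE participant at that site.

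**Start of each site.** Research Design says: "Each hospital (site) is a cluster, with the Phase 1 start time being dependent on hospital logistics". Randomisation is individual, takes place in Phase 2, and is between midwife (MW) and video (VI) instruction only.

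**Primary contrast.** Tables 1 and 4 compare exclusive breastfeeding at 4 months (EBF4M) in the Phase 1 controls with the two Phase 2 groups combined.

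**Model.** Planned Data Analysis gives a mixed-effects logistic regression "adjusted for maternal age, socioeconomic status, mode of delivery and potentially other hypothesized confounders". The a priori confounders listed after Table 4 are education, BMI, smoking, city residence, attitudes to breastfeeding and paternal support. No step, period or calendar-time term appears in either place. On site, the section says: "The mixed effects models will incorporate a site variable both as a fixed effect, addressing any inter-site differences, and as a random effect". If a site-by-intervention interaction improves the fit, a per-site analysis with the same models follows.

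**Time span.** Current Trial Status says "Recruitment began in September 2019" and expects the last primary endpoint in April 2025.

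**The concern.** Within a site, phase and time are confounded by design. Only the staggering of sites, together with some assumption about the shape of the trend, can separate an ACE effect from a change over time. That requires time to be in the model. Without it, the primary estimate is the ACE effect plus whatever else changed at that site between its two phases. Examples are care during the pandemic, growing awareness of ACE (which the article itself reports as increasing interest) and the mix of women recruited. At stake are the bias and the error rate of the headline result.

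The site terms are a second, separate problem. A fixed effect for each site already absorbs all differences in level between sites. A random intercept for the same sites has nothing left to estimate, so it cannot do the job the protocol gives it.

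**Working it through.** **Inputs from the protocol (Sample Size).** Control rate 27%, ACE rate 45%, one-sided alpha 0.05, superiority by a 5-point margin, ICC 0.01, 271 per group. This gives 271 controls against 2 × 271 = 542 ACE participants. Breastfeeding in Australia gives a second national rate, 61%.

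**1. The plan's own figure.** With unpooled variances, n = (0.27×0.73 + 0.45×0.55)(1.645 + 0.842)² / (0.18 − 0.05)² = 0.4446 × 6.18 / 0.0169 ≈ 163 per group. The number of clusters is not given. With 4 clusters (assumed), the design effect is 1 + (67.75 − 1)×0.01 = 1.67, so n ≈ 271 and power is 80%. With the 7 listed sites the design effect is 1.38 and power is 86%. The stated 271 is reproducible, but the calculation has no allowance for a time term.

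**2. Effect of an unmodelled shift.** Suppose ACE has no effect and the rate moves by d between Phase 1 and Phase 2. The size of d is assumed, because the article gives none. At d = 0, SE = √[p(1−p)(1/271 + 1/542)] = 3.3 points at p = 27% and 3.6 points at p = 61%.

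| Shift d | One-sided 5% test against 0 (base 27% / 61%) | One-sided 5% test against the 5-point margin (27% / 61%) |
|---|---|---|
| 2 points | 14.5% / 14% | 0.5% / 0.7% |
| 4 points | 32% / 30% | 2.6% / 2.7% |
| 5 points | 43% / 40.5% | 5% / 5% |
| 10 points | 89% / 89% | 43% / 41% |

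The 4-point entries use the pooled SE at the shifted rates. With the SE held at its no-shift value they become 33% and 29%, hence the range of 14–33% for 2 to 4 points.

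**3. What a time term does.** A simulation with no ACE effect used 7 equal sites with fixed site effects, ICC 0.01, about 62 months of recruitment, starts staggered over 0–36 months and 400 replicates per setting. All of these are assumptions. Rejection rates for the one-sided 5% test against zero were:

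- Without a time term: 10.5–20.5% for 5 points of total drift, and 17–47% for 10 points.
- With a linear calendar-time term: about 4–8%.

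Longer staggering gave the smaller biases. The SE of the ACE effect was 2.0–2.5 times larger with the time term.

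**4. Cost in precision and power.** A generalised-least-squares calculation for 7 sites under another assumed schedule (12-month Phase 1, 6-month gap, 24-month Phase 2, starts 3–9 months apart) gave these SEs:

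- no time term: about 3.6 points;
- time term and random site: 4.6–8.2 points;
- fixed site and categorical periods: 7.1–9.5 points.

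The inflation is therefore 4.6/3.6 ≈ 1.3 to 9.5/3.6 ≈ 2.6.

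For 27% versus 45%, the SE without a time term or design effect is √(0.27×0.73/271 + 0.45×0.55/542) = 3.44 points. One-sided power against the 5-point margin is Φ(13/(f × 3.44) − 1.645), where f is the inflation factor:

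| f | 1.0 | 1.3 | 1.5 | 2.0 | 2.5 | 2.6 |
|---|---|---|---|---|---|---|
| Power | 98% | 90% | 81% | 60% | 45% | 42% |

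Power falls below 80% once the SE is about 1.5 times larger.

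**5. Site entered twice.** In a linear-model check with fixed site effects, the random-intercept variance was set to 0, 0.0001, 0.001 and 0.01. The REML log-likelihood was 240.107 at each value, and ML was highest at zero. The ACE estimate (0.0311) and its SE (0.0335) did not change. The random intercept is not identified and adds no allowance for correlation. It also leaves the estimate alone, so it is not the source of the drift bias.

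**The case against.** **The covariate list is open, and the full analysis plan is not shown.** This is fair, and time could still be added. But the article fixes the model form, named covariates, site structure, interaction test and per-site analysis, and it lists its confounders. Time is in none of these.

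**The modelling sentence covers breastfeeding at 1 to 16 weeks, which Table 4 assigns to MW versus VI.** Applying it to the primary contrast is an inference, though a reasonable one. The abstract promises adjusted logistic regression for ACE instruction and breastfeeding outcomes, and no other model is given.

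**Drift has no documented size.** This stands. The article calls national rates consistent since 2014–15, but those surveys precede recruitment. It also warns against comparing the 2020–21 survey with earlier ones. Stability is neither shown nor refuted.

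**The protocol uses a 5-point margin.** This stands and matters. Against the margin with no ACE effect, shifts of 2–4 points give only 0.5–2.7% false positives. The higher rates apply if the general p < 0.05 criterion means a test against zero. The bias in the estimate is the same either way.

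**The sequential design is disclosed, with contamination as its reason.** This is also true, and it justifies the design. It does not supply the missing term.

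A reader might infer several stronger things that the article does not support:

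- *All drift from 2019 to 2025 is credited to ACE.* Only the change between a site's own two phases is.
- *The double site term causes the drift bias.* It does not (step 5).
- *Fixed site effects waste the staggering.* With a time term they still use it. They lose only the cross-sectional comparison between sites, which is itself confounded because start order follows logistics.
- *The Limitations section claims that time trends act equally.* Its statement that "it is expected that the limitations will affect all three groups equally" introduces language, recall and masking, and makes no claim about time.

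**Conclusion.** The concern holds. As written, the primary analysis cannot distinguish ACE from any other change between a site's Phase 1 and Phase 2, and the contrast is not randomised at either individual or site level. This needs correcting before analysis because it affects the headline estimate.

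The direction and size of the bias are unknown. The 14–33% false-positive range is conditional on an assumed shift of 2–4 points and a test against zero. The precision and power figures depend on assumed site schedules. The sample size of 271 per group is not itself wrong on this point.

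The redundant random site intercept is a lesser and independent fault. The MW-versus-VI comparison is concurrent and randomised, so the time confounding does not touch it.

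**What to change.** 1. Prespecify a calendar-time adjustment, based on date of birth, in the primary control-versus-ACE model. Keep it parsimonious: a linear term, a spline with few degrees of freedom, or broad periods. With at most seven sites, fine time categories plus random site-by-period effects may be barely estimable.
2. Keep one site term, fixed or random. Use small-sample inference, or inference robust to cluster-by-period correlation, where it can be estimated.
3. Treat the unadjusted comparison of proportions, and any per-site control-versus-ACE analysis, as descriptive. One site cannot separate phase from time.
4. Describe control versus ACE as a non-randomised staggered comparison, and reserve the word randomised for MW versus VI.
5. Restate the power for control versus ACE under the time-adjusted model, using the actual site start dates, the one-sided alpha and the 5-point margin.

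The cost is wording in the protocol and analysis plan, plus use of the infants' dates of birth, which should be available from the medical records already accessed. The confidence interval will be wider and the stated power less favourable, possibly below 80%.
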